## Abstract

**Background:**

Workplace mental health promotion (WMHP) aims to prevent and effectively manage the social and economic costs of common mental illnesses such as depression. The mental health of managers and employees within small-medium enterprises (SMEs) is a neglected sector in occupational health research and practice, despite the fact that this sector is the most common work setting in most economies. The availability and propensity of SME staff to attend face-to-face training/therapy or workshop style interventions often seen in corporate or public sector work settings is a widely recognised problem. The 'Business in Mind' program employs a DVD mode of delivery that is convenient for SME managers, particularly those operating in regional and remote areas where internet delivery may not be optimal. The objective of the intervention program is to improve the mental health of SME managers, and examine whether employees of managers' whose mental health improves, report positive change in their psychosocial work environment. The mechanisms via which we aim to improve managers' mental health are through the development of their psychological capital (a higher order construct comprised of hope, self efficacy, resilience and optimism) and their skills and capacities for coping with work stress.

**Methods/Design:**

The effectiveness of two versions of the program (self administered and telephone facilitated) will be assessed using a randomised trial with an active control condition (psychoeducation only). We aim to recruit a minimum of 249 managers and a sample of their employees. This design allows for 83 managers per group, as power analyses showed that this number would allow for attrition of 20% and still enable detection of an effect size of 0.5. The intervention will be implemented over a three month period and postal surveys will assess managers and employees in each group at baseline, intervention completion, and at 6 month follow up. The intervention groups (managers only) will also be assessed at 12 and 24 month follow-up to examine maintenance of effects. Primary outcomes are managers' levels of psychological capital (hope, resilience, self-efficacy and optimism), coping strategies, anxiety and depression symptoms, self-reported health, job satisfaction and job tension. Secondary outcomes are participating managers subordinates' perceptions of manager support, relational justice, emotional climate and job tension. In order to provide an economic evaluation of the intervention, both employees and manager rates of absenteeism and presenteeism will also be assessed.

**Discussion:**

The intervention being trialled is expected to improve both primary and secondary outcomes. If proven efficacious, the intervention could be disseminated to reach a much larger proportion of the business community.

**Trial registration:**

Current controlled trials ISRCTN 62853520

## Background

The World Health Organization (WHO) predicts that depression will be ranked as the second largest cause of burden of disease by 2020. The disorders grouped under the generic category 'depression' are the most prevalent psychiatric conditions, with individual lifetime risk estimates ranging between 20–55% [1] In addition to its considerable social impact, depression has significant economic costs related to work performance [2-4], workplace safety, absenteeism, and early retirement [5]. Accordingly, workplace mental health promotion programs are becoming more widespread, but still lack accumulated empirical evidence of their effectiveness.

Research indicates that the early identification of depression symptoms and the provision of encouragement to seek treatment are cost-effective methods for increasing employee well-being [6]. However, it is often argued that we need to go further, by examining those aspects of work and work environments which promote or detract from mental health [7]. There is now a strong body of longitudinal evidence that causally implicates aspects of the work environment in the development of health conditions such as depression (see recent reviews [8,2,9]). Managerial style has been identified as a core concern in occupational health research. For example, managers' lack of support and inconsiderate or hostile behaviour contributes directly to employee depression [10]. The relationship between employee reports of unfair treatment from supervisors and their subsequent increased risk of developing psychiatric problems are observed even when individual dispositions and demographic characteristics are controlled for [11].

The ability of managers to provide social support and create a positive work environment is negatively impacted when their own mental health is compromised. Managers experiencing symptoms of depression are more prone to aggressive behaviour and other forms of abusive supervision [12] and are less likely to be inclined to provide support to employees [13]. This is a significant problem as depression is currently at above average levels among managers. Prevalence rates for DSM-IV depression diagnoses in the Australian National Mental Health Survey were higher among managers than any other occupational group [14]. Another study in the United Kingdom showed that a third of managers undergoing organizational changes reported mental health levels comparable to, or worse than, psychiatric outpatients [10]. While a small proportion of managers may formally meet the diagnostic criteria for depression, a larger number will experience sub-threshold levels of depression symptoms and high levels of occupational stress which affect their behaviour towards employees. Even if managers are not depressed, their transient negative mood states, such as anger and sadness, affect employees through a process theorized as 'emotional contagion' [15]. Accordingly, researchers have called for more research on the impact of leader emotions and behaviour on employee well-being [16].

Studies of employee psychological distress have typically classified depression as an outcome of the work environment (e.g., [12]). In addition to manager's mental health being a key outcome, in the current research the mental health of the manager is also classified as an *independent *variable that is associated with employee well-being. Thus, in addition to directly improving the psychological health of managers, our intervention is also designed to enhance the psychosocial work environment, thereby reducing employees' risk of experiencing occupational stress and depression.

### Focus on SMEs

Recent Australian research indicated that while 43% of managers agreed that depression was a topic suitable for discussion in the workplace, only 25% had received any training from their organization on mental health issues, and only 33% had a clear policy on mental health [13]. These problems were particularly pronounced in SMEs. Occupational epidemiologists have suggested that SMEs need "special attention because their knowledge, competence and financial resources to carry out interventions are limited" ([17], p. 95). Strategies that are routinely employed by larger organizations such as Employee Assistance Programs, mental health literacy workshops, or stress management training are difficult to implement and are infrequently adopted by SMEs. Smaller organizations also provide an excellent setting for the study of emotional contagion as SME employees are often more proximal to the emotions of their managers. Hence, the leader's influence on the work group's affective climate may be a significant determinant of employee well-being within SMEs. In an era of constrained expenditure on healthcare services, this is anticipated to be a cost-effective method of mental health promotion. In addition, economic evaluation of workplace mental health promotion is rare, and almost non-existent for programs delivered in SMEs [18]. This research will also directly evaluate the cost-effectiveness of the intervention to SMEs using measures of absenteeism and presenteeism designed for this sector. Clearly, the SME sector needs urgent attention in relation to occupational health research and practice [19].

### Aims of the research

Our study aims to describe the efficacy of a mental health promotion intervention for enhancing the mental health of SME managers and investigate the processes by which the psychological state of managers affects their subordinate's well-being via the workplace psychosocial environment. In summary, our research will test the hypothesized theoretical model shown in Figure 1. In addition, we will calculate the cost-effectiveness of this intervention in order to guide policy and decision-making by our research partners, business stakeholders and government bodies.

**Figure 1 F1:**
[figure not shown]
**Proposed Theoretical Model**.

## Methods/Design

### Study Design

The research design employed a three arm randomized controlled trial including 249 managers (83/83/83 – see power calculations below). The trial is also evaluated using a sample of employees of each of these managers (estimated to be approximately 2490 employees). Measurements are scheduled at baseline, directly after completion of the intervention, and at 6 months follow up. After this time the managers in the control group will be offered the intervention on a self administered basis (see intervention delivery below). Longer-term follow up measures at 12 and 24 months post intervention will examine changes in managers' risk for depression and the potential for the intervention to protect or 'inoculate' them during significant work or life challenges. Figure 2 presents the flow chart representing the study design.

**Figure 2 F2:**
[figure not shown]
**Study Design Flowchart**.

### Recruitment of participants

We aim to recruit a minimum of 249 managers within SMEs throughout one state of Australia (Tasmania). Managers will primarily be drawn from the networks of three partner organizations collaborating with this research (*beyondblue *– the Australian national depression initiative, Workcover – a statutory occupational health and safety body and the Chamber of Commerce and Industry – a local business association). A mailing list of approximately 1250 managers of SMEs has been compiled from these networks. Cross-sectional self-report surveys of managers obtain an average response rate of 30% [20]. However, given the longitudinal and intervention requirements of this research it is conservatively estimated that 20% of the 1250 managers invited will participate (N = 250 at baseline). Adjusting for attrition we anticipate a sample size of N = 200 at post intervention assessment. Employing Cohen's (1992) formula, a 3 group ANOVA with an effect size of 0.5 would provide a power of 0.8 (*a *= 0.05) with 156 participants (52 per group). We based our anticipated effect size of 0.5 on two meta-analyses [21,22].

Information about the study will also be provided in the media and via local small business associations and potential participants will be invited to contact the research team for more information about the study. To be included, participants must have a managerial role within a business employing less than 200 employees, be over 18 years of age and have access to a telephone and computer/DVD player.

We also aim to recruit an estimated 2490 employees representing workers in SMEs. Participating managers will be asked to facilitate the distribution of research invitations for their employees. Recruitment of employees will be undertaken by the researchers, hence, the decision to participate in the research will be made confidentially by the employees (managers will not know if their employees are participating). All employees of participating managers will be invited to participate. We have based our estimate of the employee sample size on approximately 10 employees per manager agreeing to participate. Small businesses generally employ less than 20 employees and medium sized businesses generally employ less than 200. Whilst it is difficult to estimate, statistics within the region in which we are recruiting indicate that the largest proportion of businesses represented is likely to be categorised as small. As staff turnover in small businesses is expected to be reasonably high, the follow up will be limited to 6 months post-intervention. All participants will be offered the chance to enter a prize draw as an incentive for continued participation.

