### Data analysis

The primary data analysis will compare the efficacy of the two intervention treatment conditions in comparison to the active control group, based on differences in manager's mental health, psychological capital, and work outcomes. Evaluation will be based on an intent-to-treat analysis. A generalised estimating equations approach using the SAS statistical package will be employed. This approach enables the inclusion of all available data including participants who are lost to follow-up or who have incomplete data. Secondary data analyses will test for differences across the groups in employee mental health and perception of the psychosocial work environment, with adjustment for clustering if necessary. Reasons for treatment success/failure will be identified also via a process evaluation framework. An economic evaluation will estimate the incremental cost-effectiveness of the two intervention treatment conditions in comparison to the active control, from both a societal and employer perspective to ensure direct relevance to the SME context. Indirect costs will include lost productive time from absenteeism and presenteeism. Economic analysis will be informed by another of our studies currently underway which is estimating the societal and employer costs associated with depression in the Australian workforce [3].

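### The stated power of 0.8 with 52 per group is wrong for an effect size of 0.5, whether 0.5 is read as Cohen's f or as a 0.5 SD difference; the planned 249 is not thereby shown to be too small

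*Protocol article*

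**What the plan says.** The protocol article gives one power calculation, under Recruitment of participants. It is introduced by "Employing Cohen's (1992) formula" and states that "a 3 group ANOVA with an effect size of 0.5 would provide a power of 0.8" at alpha 0.05 "with 156 participants (52 per group"). The source of the effect size is given as follows: "We based our anticipated effect size of 0.5 on two meta-analyses [21,22]". Neither sentence says whether 0.5 is a standardised mean difference (Cohen's d) or the ANOVA measure (Cohen's f).

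The same paragraph expects about 250 managers at baseline (20% of 1250 invited) and 200 at the post-intervention assessment.

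Study Design describes a "three arm randomized controlled trial including 249 managers (83/83/83") and points the reader to the power calculations. The Abstract says that "power analyses showed that this number would allow for attrition of 20% and still enable detection of an effect size of 0.5", where the number meant is 83 per group.

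Under Data analysis, the planned comparison is this: "The primary data analysis will compare the efficacy of the two intervention treatment conditions in comparison to the active control group".

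**The concern.** The sentence gives the test, the number of groups, the effect size, alpha, power and sample size, so it can be checked. The combination is not possible for a three-group ANOVA under either usual meaning of 0.5. It looks as if f = 0.25 was equated with d = 0.5. That conversion (f = d/2) holds for two equal groups but not for three. This explanation is an inference; the mismatch is not.

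What is at stake is how the trial's safety margin is read. Setting 200 expected completers beside 156 needed suggests a cushion of 44 managers. Someone who judged retention against 156 would believe the trial still had 80% power for a 0.5 SD difference when, without covariate adjustment, it would not. The calculation also describes an omnibus test, while the planned primary comparison sets each intervention against control.

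**Working it through.** **Inputs from the protocol article.** Three groups, effect size 0.5, alpha 0.05, power 0.8, 52 per group (Recruitment of participants); 83 per group (Study Design); 20% attrition (Abstract). Completers per arm: 83 × 0.8 = 66.4, about 66.

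**Method.** For a one-way ANOVA with k = 3 groups of n, power is the probability that a noncentral F with 2 and 3n − 3 degrees of freedom and noncentrality λ = 3n·f² exceeds the 5% critical value. At n = 52 the degrees of freedom are 2 and 153, and the critical value is 3.055.

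**Reproducing the plan's figure.** With f = 0.25, λ = 156 × 0.0625 = 9.75 and power is 0.797. This matches the stated 0.8 (53 per group reaches 0.80 exactly or better). So 52 per group corresponds to f = 0.25.

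**Reading 1: 0.5 is Cohen's f.** λ = 156 × 0.25 = 39 and power is 0.9999. For 80% power, 14 per group suffice.

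**Reading 2: 0.5 is the largest difference between two arm means, in SD units.** Here f is the standard deviation of the three means (divisor 3):
- third arm midway (0, 0.25, 0.5): f = 0.5 × √(1/6) = 0.204
- two arms equal (0, 0.5, 0.5 or 0, 0, 0.5): f = 0.5 × √2/3 = 0.236

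| Pattern of means | f | λ at n = 52 | Power at 52 | n per arm for 80% | Power at 66 |
|---|---|---|---|---|---|
| Third arm midway | 0.204 | 6.50 | 0.612 | 79 | 0.725 |
| Two arms equal | 0.236 | 8.67 | 0.745 | 59 | 0.847 |

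Turned round, f = 0.25 in three arms is a largest difference of 0.25/0.236 = 0.53 SD (two arms equal) to 0.25/0.204 = 0.61 SD (third arm midway).

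**Each intervention against control.** Two-sided t-test, d = 0.5, noncentrality d·√(n/2), no covariate adjustment:
- n = 52: noncentrality 2.55, power 0.714
- n = 64: noncentrality 2.83, power 0.80 (the smallest n that reaches it)
- n = 66: noncentrality 2.87, power 0.814

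If alpha were split to 0.025 for each of the two contrasts, which the article does not say, power at 66 would be 0.727.

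**The margin.** Stated: 200 − 156 = 44. For the pairwise contrasts at d = 0.5: 3 × 64 = 192, so 200 − 192 = 8. For the omnibus test: 3 × 59 = 177 to 3 × 79 = 237, so anything from 23 to spare to 37 short.

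**Effect of baseline adjustment.** The baseline correlation r is assumed; the article gives none. Scaling the variance by 1 − r², pairwise power at d = 0.5 is:

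| r | 52 per arm, alpha 0.05 | 66 per arm, alpha 0.025 |
|---|---|---|
| 0.3 | 75% | 77% |
| 0.6 | 88% | 91% |

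**The case against.** The strongest reply is that the trial does not plan 52 per group. It plans 83, with about 66 completers, and reaches 52 only at 1 − 52/83 = 37% attrition, nearly twice the assumed rate. This stands. A reader might infer that the trial itself has only 61% to 75% power. The article does not support that, because those figures belong to 156 completers.

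A second reply is that all the figures above are unadjusted, single-time-point tests, whereas Data analysis plans generalised estimating equations on repeated measurements. This stands in part. With a baseline correlation of 0.6, even 52 per arm would give 88% for a pairwise contrast; with 0.3, it would give 75%. But the article states neither a correlation nor a baseline adjustment, and its sample-size paragraph relies on neither. For the same reason, 64 completers per arm is a requirement for the unadjusted pairwise test, not a general floor.

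A third reply is that a one-sided two-group t-test at d = 0.5 with 52 per group has power 0.813. It does, but the text names a three-group ANOVA.

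Two further inferences are tempting and fail:
- **65 against 83.** Inflating 52 for 20% attrition gives 65, so 83 may look unexplained. But the total of about 250 comes from the recruitment forecast, and the Abstract says only that 83 is enough. That is not a contradiction.
- **The Abstract's claim.** It may seem to hold only for an unadjusted pairwise contrast. But the omnibus test also reaches 85% at 66 per arm when two arms are equal, and the Abstract states no power value.

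**Conclusion.** The power sentence is wrong as written. With 52 per group, a three-group ANOVA at alpha 0.05 has power above 0.999 if 0.5 is Cohen's f, and 61% to 75% if 0.5 is the largest difference in SD units. The likelier meaning is a standardised difference, since the value is attributed to meta-analyses, but the article does not say so. An unadjusted pairwise comparison has 71%.

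The consequence is limited. Most of the cushion between 156 and 200 disappears on the unadjusted pairwise requirement, but the planned size gives 81% for one such contrast at two-sided 0.05 and 72% to 85% for the omnibus test. These results assume normal outcomes with equal variance, equal arms, completers only and no covariate adjustment. The point should be fixed, but it is no reason to change enrolment.

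**What to change.** Keep enrolment at 249. In the sample-size paragraph:
- State whether 0.5 is Cohen's d or Cohen's f.
- Replace the 156/52 sentence with the power of the planned comparisons at the planned size. If 0.5 is Cohen's d, for example: about 66 completers per arm give 81% power for a 0.5 SD difference between each intervention and control, two-sided alpha 0.05, without covariate adjustment.
- If alpha is to be split across the two contrasts, say so and give 73% instead.
- If a gain from baseline adjustment is claimed, show it as a range over assumed correlations, such as 77% at r = 0.3 to 91% at r = 0.6 for 66 per arm at alpha 0.025.
- Word the Abstract to match.

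The cost is the rewording of one paragraph and one Abstract sentence. The stated margin becomes smaller; recruitment, design and analysis do not change.

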### Treatment allocation

Randomization by computer will assign managers (and their associated subordinates) to either the experimental or control conditions. No blocking or stratification procedures will be employed as all willing participants who meet the basic inclusion criteria will be eligible for assignment after informed consent is received. Those currently receiving treatment for a mental health disorder will be identified and examined in the final analyses.

## Description of intervention

### Intervention content

The intervention consists of the '*Business in Mind*' DVD program (60 minutes) and accompanying guidebook. The intervention involves skills development using a Cognitive Behaviour Therapy framework and contains four modules. The first module aims to develop participants' understanding of stress and coping processes, introducing the relationships among thoughts, feelings and behaviours. The second module is designed to enhance participants' level of 'psychological capital' (PsyCAP). PsyCAP is a construct drawn from the positive psychology movement and is characterized by the indicators of self efficacy, hope, resilience and optimism. PsyCAP interventions utilize processes of reflection, goal design, pathway generation, overcoming obstacles, role modeling, and the facilitation of preparedness and mastery [23-25]. Module three is focused on overcoming barriers to living a healthy lifestyle and covers topics such as physical activity, nutrition, substance abuse and creating an effective work-life balance. The final module focuses on assisting managers to create a positive work environment and overcome interpersonal stressors by developing their emotional intelligence and communication skills.

The DVD shows real managers sharing their work experiences and demonstrating their skills. The guidebook contains structured tasks and handouts that help participants apply the ideas presented in the DVD to their own situations. An associated password protected website also links participants with additional resources to help them further their personal development. Participants will be given a three month timeline to complete the program.

